### **5.3.2 Adherence and medication use**

For this study adherence is defined as taken at least 80% of alendronate in both treatment periods of 12 weeks and is evaluated by pill counts. The amount of Caci-chew D3 tablets taken will be counted but is not incorporated in the assessment of adherence.

Medication use and adherence are evaluated by the Self-efficacy for Appropriate Medication Use (SEAMS) Questionnaire and the Brief Medication Questionnaire (BMQ) respectively. The SEAMS is a reliable and valid instrument based on 13 questions that may provide a valuable assessment of medication self-efficacy in chronic disease management, and appears also appropriate for use in patients with low literacy skills. This questionnaire will be assessed at week 4, 12, 16 and 24. For detailed information see appendix 2.

The BMQ appears more sensitive than other existing tools and may be useful in identifying and diagnosing adherence problems. It will be assessed at visit week 4, 12, 16, 24. For detailed information see appendix 3.

#### **5.4 Evaluation of Bone markers**

The serum sample for CTX (sCTx bij Roche Elecsys), will be obtained at ay 1, week 4, 12, 16 and 24. SCTx should be collected before 10:00 am and subjects should fast overnight before blood sample collection. A second urine morning sample will be collected at the same time. The samples have to be transported on ice and must be frozen within 1 hour. The results will be expressed in absolute values and in Z-scores.

#### **5.5 Evaluation of blood chemistry**

Serum calcium, phosphate, albumin, 25 OH vitamin D, PTH, Sodium, potassium, kreatinine and Hb will be collected together with sCTx at the same venous puncture (15 ml at each visit 1,2,3,4 and 5).

### **6. STUDY PROCEDURES**

See schedule 6.1

## 6.1 Schedule of Evaluations

| Assessment                                    | Screening: Visit-1
(Day-14 to Day -1) | Baseline, Enrollment,
Randomization: Visit 1 (Day 1) | Treatment
Visit 2 (W4) | Treatment
Visit 3 (W12) | Treatment
Visit 4 (W16) | Final Visit
Visit 5 (W24) |
|-----------------------------------------------|------------------------------------------|---------------------------------------------------------|---------------------------|----------------------------|----------------------------|------------------------------|
| Informed Consent Form         | X                                        |                                                         |                           |                            |                            |                              |
| Demographics                  | X                                        |                                                         |                           |                            |                            | X                            |
| Medical History               | X                                        |                                                         |                           |                            |                            |                              |
| Inclusion/Exclusion Criteria  | X                                        | X                                                       |                           |                            |                            |                              |
| Enrollment/Randomization      |                                          | X                                                       |                           |                            |                            |                              |
| Concomitant Medications       | X                                        | X                                                       | X                         | X                          | X                          | X                            |
| General Physical Examination  | X                                        | X                                                       |                           |                            |                            | X                            |
| Vital signs                   | X                                        | X                                                       |                           | X                          |                            | X                            |
| Blood Chemistry               |                                          | X                                                       |                           | X                          |                            | X                            |
| Bone markers                  |                                          | X                                                       | X                         | X                          | X                          | X                            |
| Urine Analysis                |                                          | X                                                       | X                         | X                          | X                          | X                            |
| Treatment Administration Form |                                          | X                                                       | X                         | X                          | X                          | X                            |
| GSRs Questionnaire            |                                          | X                                                       | X                         | X                          | X                          | X                            |
| SEAMS Questionnaire           |                                          |                                                         | X                         | X                          | X                          | X                            |
| BMQ Questionnaire             |                                          |                                                         | X                         | X                          | X                          | X                            |
| Adverse Events                |                                          | X                                                       | X                         | X                          | X                          | X                            |

## 6.2 Description of Evaluations

### 6.2.1 Study Visit Definitions

- The screening date is defined as the date the informed consent is signed.
- Enrolment date is defined as the date of randomization.
- Day 1 is defined as the day that brand or generic alendronate is dispensed to the subject.
- A study month is defined as a calendar month.
- Randomization must occur within 14 days of the screening and Day 1 must be completed within 72 hours of randomization.
- All on-study (post Day 1) visits should be scheduled from the initial Day 1 visit calendar date. For example, if a subject's Day 1 visit is January 15, then their Month-6 visit should be targeted to occur on July 15.
- If a subject's visit is delayed, their subsequent visit dates should not be shifted, but always calculated based on the Day 1 visit date.

### 6.2.2 Study Visit Windows

All tests and procedures scheduled for Day 1 must occur within 72 hours of the randomization date.

All tests and procedures scheduled for the Week 4, 12, 16 and Week 24 visits must be performed within  $\pm 7$  days of the scheduled visit date.

Any missed visits, tests not done and examinations not conducted must be reported as such.

Study procedures for a specific visit may be completed on multiple days as long as all of the procedures are completed within the visit window.

### 6.2.3 Study visit description

#### Screening

Screening and Day-1 visit cannot occur on the same day.

The following assessments will be performed at screening:

- Sign Informed Consent Form

After signing the informed consent form:

- Key baseline risk characteristics
- Medical and medication history
- Vital signs (including blood pressure and pulse)
- Physical examination
- Determine eligibility

#### Day 1 Visit (within 72 hours of randomization date)

The following assessments will be performed at Day 1 (all Day-1 procedures must be completed prior to administration of brand or generic alendronate):

- Randomize the subject and obtain treatment assignment
- Vital signs (including blood pressure and pulse)
- Physical Examination (including height and weight)
- Laboratory samples
- Concomitant medication recording
- Adverse event collection
- Administration of GSRS
- Brand or generic alendronate dispensed to subject

#### Week 4 visit ( $\pm$ 7 days)

- Vital signs (including blood pressure and pulse)
- Laboratory samples
- Concomitant medication recording
- Administration of GSRS, SEAMS and BMQ
- Adverse event collection

**Week 12 visit ( $\pm$  7 days)**

- Vital signs (including blood pressure and pulse)
- Physical Examination (including height and weight)
- Administration of GSRS, SEAMS and BMQ
- Laboratory samples
- Concomitant medication recording
- Adverse event collection
- Study drug accountability
- Brand or generic alendronate dispensed to subject (cross-over)

**Week 16 visit ( $\pm$  7 days)**

- Vital signs (including blood pressure and pulse)
- Laboratory samples
- Concomitant medication recording
- Administration of GSRS, SEAMS and BMQ
- Adverse event collection

**Week 24 FINAL visit ( $\pm$  7 days)**

- Vital signs (including blood pressure and pulse)

- Physical Examination (including height and weight)
- Administration of GSRS, SEAMS and BMQ
- Laboratory samples
- Concomitant medication recording
- Adverse event collection
- Study drug accountability

#### **6.2.4 Impact and duration of study visits on participating subjects**

There will be a total number of 6 study visits during a total period of 26 weeks. Each visit takes approximately 30 minutes, so the total study visit time per subject will be 180 minutes. During the study there will be 3 general physical examinations, 5 blood collections, each 15ml (total amount 75 ml, for bone markers and chemistry) and 5 urine collections. Participants have to complete a total number of 13 questionnaires throughout the study.

## **7. REMOVAL AND REPLACEMENT OF SUBJECTS**

### **7.1 Removal of Subjects**

Subjects have the right to withdraw fully or partially from the study at any time and for any reason without prejudice to his or her future medical care by the physician or at the institution.

Withdrawal of full consent for a study means that the subject does not wish to receive further investigational treatment and does not wish to or is unable to continue further study participation. Any subject may withdraw full consent to participate in the study at any time during the study. The investigator will discuss with the subject the most appropriate way to withdraw to ensure the subject's health.

Withdrawal of partial consent means that the subject does not wish to take the investigational product any longer but is still willing to collaborate in providing further data by continuing on study (eg, participate in all subsequent study visits or procedures). Subjects may decline to continue receiving the investigational product at any time during the study. These subjects, as well as those who have stopped receiving the investigational product for other reasons (eg, investigator or sponsor concern) will be asked to participate in one, last visit for completion of the data.

Reasons for removal from the investigational product or study might include:

- administrative decision by the investigator

- ineligibility
- significant protocol deviation
- patient noncompliance
- adverse event
- withdrawal of consent

Should a subject (or a legally acceptable representative) request or decide to withdraw from the study, all efforts will be made to complete and report the observations as thoroughly as possible up to the date of withdrawal. If withdrawn consent is recorded as the reason for either ending investigational product or ending study an attempt should be made to determine the possible underlying reason for withdrawing consent, if applicable, and to record that as the primary reason. All information should be reported.

In addition, if a subject experiences an osteoporosis-related fracture (eg, crush vertebral fracture, hip fracture), the investigator should evaluate the situation and discuss alternative treatment options with the subject.

## **7.2 Replacement of Subjects**

Enrolled subjects who have been removed from this study will not be replaced.

# **8. SAFETY ASSESSMENTS**

## **8.1 Section 10 WMO event**

In accordance to section 10, subsection 1, of the WMO, the investigator will inform the subjects and the reviewing accredited METC if anything occurs, on the basis of which it appears that the disadvantages of participation may be significantly greater than was foreseen in the research proposal. The study will be suspended pending further review by the accredited METC, except insofar as suspension would jeopardise the subjects' health. The investigator will take care that all subjects are kept informed.

## **8.2 Adverse Events**

An adverse event is defined in the International Conference on Harmonisation (ICH) Guideline for Good Clinical Practice as “any untoward medical occurrence in a patient or clinical

investigation subject administered a pharmaceutical product and that does not necessarily have a causal relationship with this treatment.” (ICH E6:1.2)

This definition of adverse events also includes worsening of a pre-existing medical condition. Worsening indicates that the pre-existing medical condition (eg, cancer, diabetes, migraine headaches, gout) has increased in severity, frequency, or duration of the condition or an association with significantly worse outcomes.

The occurrence of a fracture will be assessed at visit week 4, 12, 16 and 24 and will be reported as adverse event.

Interventions for pretreatment conditions (eg, elective cosmetic surgery) or medical procedures that were planned before study enrollment are not considered adverse events

The investigator is responsible for reviewing laboratory test results and determining whether an abnormal value in an individual study subject represents a change from values before the study. In general, abnormal laboratory findings without clinical significance (based on the investigator's judgment) should not be recorded as adverse events; however, laboratory value changes requiring therapy or adjustment in prior therapy are considered adverse events.

### **8.3 Serious Adverse Events**

A serious adverse event (SAE) is defined as an adverse event that

- is fatal
- is life threatening (places the subject at immediate risk of death)
- requires in-patient hospitalization or prolongation of existing hospitalization
- results in persistent or significant disability/incapacity
- is a congenital anomaly/birth defect
- other significant medical hazard

A hospitalization meeting the regulatory definition for “serious” is any inpatient hospital admission that includes a minimum of an overnight stay in a health care facility. Any adverse event that does not meet one of the definitions of serious (eg, emergency room visit, outpatient surgery, or requires urgent investigation) may be considered by the investigator to meet the “other significant medical hazard” criterion for classification as a serious adverse event. Examples include allergic bronchospasm, convulsions, and blood dyscrasias.

### **8.4 Premature termination of the study**

In addition of paragraph 8.1 the study will be terminated when (serious) adverse event or other disadvantages occur more often than foreseen or currently known during treatment with either one of the study drugs.

## 8.5 Reporting Procedures

The investigator is responsible for ensuring that all adverse events (as defined in 8.1 and 8.2) observed by the investigator or reported by subjects are collected and recorded in the subjects' medical records. These adverse events will include the following:

The following adverse event attributes must be assigned by the investigator: adverse event diagnosis or syndrome(s) (if known, signs or symptoms if not known); event description (with detail appropriate to the event); dates of onset and resolution; severity; assessment of relatedness to investigational product and action taken.

If applicable, the relationship of the adverse event to the investigational product will be assessed by means of the question: "Is there a reasonable possibility that the event may have been caused by the investigational product?" The investigator should respond to this question with either Yes or No.

The severity grading scale used in this study is described in Appendix B.

Medically significant adverse events considered related to the investigational product by the investigator will be followed until resolved or considered stable.

It will be left to the investigator's clinical judgment to determine whether an adverse event is related and of sufficient severity to require the subject's removal from treatment or from the study. A subject may also voluntarily withdraw from treatment due to what he or she perceives as an intolerable adverse event. If either of these situations arises, the subject should be strongly encouraged to undergo an end-of-study assessment and be under medical supervision until symptoms cease or the condition becomes stable.

Procedures with regard to SUSARS (Suspected unexpected serious adverse reactions):

The investigator will report expedited the following SUSARs to the METC (Maastricht UMC) and CEM (Viecuri Venlo):

- SUSARs that have arisen in the clinical trial that was assessed by the METC and CEM;
- The remaining SUSARs are recorded in an overview list (line-listing) that will be submitted once every half year to the METC. This line-listing provides an overview of all SUSARs from the study medicine, accompanied by a brief report highlighting the main points of concern.

The expedited reporting will occur not later than 15 days after the investigator has first knowledge of the adverse reactions. For fatal or life threatening cases the term will be maximal 7 days for a preliminary report with another 8 days for completion of the report.

The Medical research involving human subjects Act is applicable for (subjects participating in) this study.

In addition to the reporting of SUSARs, the investigator will submit, once a year throughout the clinical trial, a continuity report to the METC (appendix 9).

After completion of the study the termination form will be completed and reported to the METC within 90 days (appendix 10).

## **8.6 Insurance**

The sponsor/investigator has a liability insurance which is in accordance with article 7, subsection 6 of the WMO.

The sponsor (also) has an insurance which is in accordance with the legal requirements in the Netherlands (Article 7 WMO and the Measure regarding Compulsory Insurance for Clinical Research in Humans of 23th June 2003). This insurance provides cover for damage to research subjects through injury or death caused by the study. (appendix 7)

## **9. STATISTICAL CONSIDERATIONS**

The hypothesis tested in this trial is a non-inferiority in efficacy based on the outcome parameter: serum CTx resorption bone marker at visit 3 and 5 (week 12 and week 24) of both treatment groups.

De CTx outcome will be expressed in standardized Z-scores. Z-scores can be used to compare a measurement to a reference value. The Z-score is the number of standard deviations away from the average value of the age and gender specific reference group (i.e. women of the same age). A difference < 0.5SD (in terms of serum Ctx Z-scores) between brand and generic alendronate is considered not to be clinically relevant.

Sample size is calculated ( $N = (Z_{\alpha} + Z_{\beta})^2 \cdot Sd^2 / d^2$ ; paired observations) based on  $\alpha = 0.05$  (95% confidence interval),  $\beta = 0.1$  (power 90%), with a standard deviation of sCTx measurements of 0.5 SD (S) and d as the difference between the mean of both treatment groups. Considering a serum CTx Z-score difference of < 0.5 SD between both groups as not clinically relevant, a sample size of 30 patients is needed to test the non-inferiority hypothesis.

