It has been suggested that there are differences in persistence between different weekly oral bisphosphonate therapies, particularly a poor persistence for patients started on generic alendronate. In one study a higher incidence in gastro-intestinal side effects was reported in patients treated with generic alendronate as compared to those treated with original once weekly bisphosphonates. In a recently published paper the persistence of patients treated with generic alendronate was significantly lower as compared to those with branded alendronate. The total numbers of patients reporting gastrointestinal adverse events with generic alendronate was more than twice the number treated with Fosamax®. There was a significantly lower increase of lumbar spine and total hip BMD with generic alendronate compared to Fosamax®. The reasons for the 40–50% lower BMD increase rates when using the generic compound is not known yet. At least in part the lower efficacy can be explained by a significantly lower degree of persistence with generic alendronate, which could be related to a higher incidence of gastrointestinal side events. Other reasons could

be the lower bioavailability or potency of generic alendronate.

Based on these results it is postulated that rapid disintegration may enhance esophageal drug exposure leading to more gastro-intestinal side effects with a possible lower degree of persistence. On the other hand, longer disintegration times may result in altered, possibly delayed or impaired absorption of alendronic acid. Since absorption is less than 1% in branded alendronate there is concern about efficacy of generic formulations.

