In contrast to BMD measurements, the alteration (decrease) in resorption markers occurs in the early phase during treatment. In fact, during the first 3 months of treatment with anti-resorptive medication such as bisphosphonates a decrease of 40-60% of bone turnover markers has been demonstrated (figure 2).

[figure not shown]

Figure 2: Changes in biochemical markers expressed as mean percentage change from baseline 

The predictive value of a decreased urine NTx for fracture risk reduction was 52%, significantly better than the predictive value of 14% with femoral neck BMD. 

At present, there can be no assurance that the Generic Alendronate tablets are equivalent to the branded product in terms of efficacy and tolerability. In order to gather more information with regard to efficacy and tolerability of branded compared to generic alendronate we designed this study in postmenopausal women with osteoporosis .

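### The non-inferiority rule compares only on-treatment sCTx values, requires no fall from Day 1, and uses a 0.5 SD margin not related to the expected treatment effect

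*Protocol*

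**What the plan says.** Protocol section 9 states the aim as follows: "The hypothesis tested in this trial is a non-inferiority in efficacy". The measure is "serum CTx resorption bone marker at visit 3 and 5 (week 12 and week 24) of both treatment groups", and "De CTx outcome will be expressed in standardized Z-scores", that is, relative to women of the same age. The margin is given in one sentence: "A difference < 0.5SD (in terms of serum Ctx Z-scores) between brand and generic alendronate is considered not to be clinically relevant". No other reason for 0.5 is offered, and the mean and SD of the reference group are not stated.

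Section 3 describes two sequences of 15 women each, 12 weeks on one formulation and then 12 weeks on the other, with no untreated arm. Sections 5.4 and 6.1 schedule sCTx at Day 1 as well as at weeks 4, 12, 16 and 24. Section 4.1 admits only women without osteoporosis treatment in the preceding 12 months, so Day 1 is an untreated value. Section 9 gives it no role.

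On the size of effect to expect, section 2.2.2.2 says that in the first three months of anti-resorptive treatment "a decrease of 40-60% of bone turnover markers has been demonstrated". Section 9 does not refer to this figure.

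**The concern.** A non-inferiority result means something only if the comparator is shown, or can safely be assumed, to have worked in this trial. Here both values in the decision are on-treatment values. If neither product lowered sCTx, the true difference would be zero and the rule would be met.

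The protocol gives reasons not to take the effect for granted. Section 2.2.1.1 puts absorption below 1%, and section 5.1 makes fasting intake a requirement. Tablet counts (sections 5.2 and 5.3.2) show that tablets left the pack, not that they were taken correctly. Poor intake of both products moves the result towards the hypothesised absence of a difference.

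The margin raises a related problem. It is expressed in SDs of a reference population and nowhere translated into a share of the drug's effect. A reader of a positive result would not know whether a small loss or most of the effect had been excluded.

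**Working it through.** **Inputs from the protocol.** Margin 0.5, SD 0.5, alpha 0.05 with a "95% confidence interval", power 90%, N = 30, 15 per sequence (sections 3 and 9); expected fall 40-60% (section 2.2.2.2).

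**1. The plan's own figure.** N = (Zα + Zβ)² × Sd² / d² = (1.960 + 1.282)² × 0.5² / 0.5² = 10.5, so 11. If 0.5 is the SD of single uncorrelated measurements, Sd of the difference is 0.5 × √2 = 0.707 and N = 21.01, so 22. Neither gives 30. That is a separate matter; below, N = 30 is taken as stated and both SDs are carried.

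**2. Chance of a win.** The rule is read as: upper 95% limit of mean (generic minus brand) below 0.5, paired t, 29 df, t = 2.045, no carry-over.

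- SD 0.5: SE = 0.5/√30 = 0.0913; half-width 0.187; an observed difference up to 0.313 passes.
- SD 0.707: SE = 0.129; half-width 0.264; an observed difference up to 0.236 passes.

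Noncentral t with noncentrality (0.5 − true difference)/SE gives:

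| True loss on generic (Z) | Win, SD 0.5 | Win, SD 0.707 |
|---|---|---|
| 0 | 99.96% | 96.3% |
| 0.2 | 89% | 61% |
| 0.3 | 56% | 32% |
| 0.4 | 18% | 11% |
| 0.5 | 2.5% | 2.5% |

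The first row applies equally when both products work fully and when neither works.

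**3. The margin as a share of the effect.** Let f be the fractional fall, CV the reference SD divided by the reference mean, and z0 the mean baseline Z. The baseline mean is then (1 + CV × z0) reference means, so the effect in Z units is f × (1 + CV × z0)/CV. CV (30-60%) and z0 (0 to +1) are assumptions; only f is in the protocol.

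| f | CV | z0 | Effect (Z) | 0.5 as share |
|---|---|---|---|---|
| 40% | 60% | 0 | 0.40/0.60 = 0.67 | 75% |
| 50% | 50% | 0 | 0.50/0.50 = 1.00 | 50% |
| 50% | 50% | +1 | 0.50 × 1.5/0.50 = 1.50 | 33% |
| 60% | 30% | +1 | 0.60 × 1.3/0.30 = 2.60 | 19% |

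**4. What a Day 1 condition does.** Require that, in the 15 women on brand in period 1, the 95% interval for mean change from Day 1 to week 12 lies below zero (14 df, t = 2.145). The half-width is 2.145 × SD/√15: 0.277 for SD 0.5 and 0.392 for SD 0.707, assuming that the SD of change equals the SD of differences.

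- Neither product works: the condition is met by chance 2.5% of the time. Simulated jointly with the rule in step 2 (100,000 runs, independent errors), a win falls from 99.96% to about 2.5% (SD 0.5) and from 96% to about 2.2% (SD 0.707).
- Both work, effect 1.0 Z: the win stays at 99.97% (SD 0.5) and about 96% (SD 0.707).
- Both work, effect 0.67 Z: 99.7% (SD 0.5); about 89% instead of 96% (SD 0.707).
- If women vary more in response, so that the SD of change is 1.0, the condition alone is met 95% of the time at 1.0 Z and 68% at 0.67 Z (noncentrality = effect × √15/SD).

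**The case against.** Both products are approved and used at the registered dose. Women unable to follow the intake instructions are excluded, intake is explained at dispensing, tablets are counted at four visits, and two questionnaires address adherence and medication use. Universal poor intake would probably be noticed. This stands as a reason to think failure of both products unlikely. It does not put any such check into the rule, and none of these measures shows absorption.

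Day 1 sCTx is collected, and section 3 lists it among the efficacy evaluations, so a supportive analysis may sit in an analysis plan not seen here. A shared Day 1 value also cancels from the within-woman contrast, so leaving it out does not bias the comparison. Both points stand. A reader might infer that the design cannot show assay sensitivity at all; it can, because the data exist. What is missing is a condition on the claim, and the protocol itself fixes the time points and margin to which that condition belongs.

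A reader might also infer that the margin gives away about half the effect. The documents do not support this. Half is one assumed combination in a range of 19-75%, and even there a true loss equal to the margin wins only 2.5% of the time.

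Finally, section 2.2.1.2 reports lower BMD gains on generic and adds: "The reasons for the 40–50% lower BMD increase rates when using the generic compound is not known yet". It is tempting to use that figure as a benchmark for sCTx loss. It concerns BMD, and the same paragraph attributes the deficit at least partly to lower persistence, so it sets no threshold for this marker.

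**Conclusion.** The point holds in two parts.

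First, the stated rule cannot separate two effective products from two ineffective ones: with 30 women it is won about 96% to over 99.9% of the time at zero difference. This rests on reading the rule as an upper 95% limit below 0.5 and on an SD of differences of 0.707 or 0.5. It says what the rule would conclude if neither product worked, not that this is likely.

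Second, the margin is not related to the expected 40-60% fall, and the documents give no reference mean or SD with which to relate it. Under the assumed CVs and baseline Z it is roughly a fifth to three quarters of the effect. No single share can be stated.

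The brand-generic contrast itself is not biased by this. What is affected is how much a positive result would say about efficacy, which is the primary objective.

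**What to change.** In section 9, add that non-inferiority is claimed only if women on brand in period 1 show a fall in sCTx from Day 1 to week 12, with the 95% confidence interval of the mean change excluding zero, or excluding a larger prespecified minimum based on the 40-60% in section 2.2.2.2. Otherwise the result is declared uninformative. Zero is a low bar: with SD 0.5, a mean fall of just over 0.28 Z clears it. Without an untreated arm, the change may also contain anything else that altered after Day 1, including the calcium and vitamin D given to all. A larger minimum makes the condition more convincing but harder to meet.

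Also report, descriptively, the mean change from Day 1 in Z-score units and in percent, and 0.5 SD as a share of the observed brand fall, so that readers see what loss the margin allows. A retained-fraction condition on the conclusion is not advised. It would rest on about 15 against 15 women in period 1 and act as a second, unpowered margin.

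The cost is a few sentences and a small analysis of data already scheduled, with no new visits, samples or patients. The downside is a possible uninformative outcome even when both products work: negligible at an effect of 1.0 Z with SDs of 0.5 or 0.707, more noticeable if the effect is near 0.67 Z or responses vary widely. Removed women are not replaced (section 7.2), so fewer than 15 may contribute.
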